## Abstract

**Background:**

Ulcers of the heel in diabetes are the source of considerable suffering and cost. In the absence of specific treatments, it has been suggested that removable, lightweight fibreglass heel casts may both promote healing and reduce discomfort and pain. The aim of the study is to assess the effectiveness and cost-effectiveness of fibreglass heel casts in the management of heel ulcers.

**Methods/Design:**

This is an observer-blind, randomised controlled trial in which participants with diabetes and heel ulcers (NPUAP/EPUAP grades 2, 3 or 4 and present for 2 or more weeks) are randomised to receive either usual care plus lightweight fibreglass heel casts or usual care alone. Randomisation is undertaken by random number sequence generation incorporated as part of the electronic case record form, and is stratified by both ulcer area (less than versus equal to or greater than 1 cm^2^) and NPUAP/EPUAP grade. Participants are followed every two weeks until healing or for 24 weeks. The primary outcome measure is healing at or before 24 weeks and maintained for 4 weeks. Secondary outcomes include (*i*) *ulcer-related outcomes*: time to healing, change in ulcer area, minor and major amputation, secondary infection and (*ii*) *patient-related outcomes*: local pain, mood and function (EQ-5D), impact of the ulcer (Cardiff Wound Impact Schedule) and survival. Cost-effectiveness will be assessed using a decision analytic model to estimate costs from the perspective of the UK NHS and personal social services and health outcomes, including percent healing and Quality Adjusted Life Years gained.

Safety will be documented as adverse and serious adverse device effects.

**Discussion:**

If it is possible to confirm significant clinical benefit and/or cost-effectiveness, this would have direct implications for the management of this distressing and costly complication of diabetes

**Trial registration number:**

ISRCTN62524796 Registered 29 March 2011

## Background

Chronic ulceration of some part of the foot affects up to 15% of all people with diabetes at some stage, and is the source of considerable cost and suffering[1]. The average age at presentation is 67 years and many of those affected are thus older aged, with significant co-morbidities and often clinging to an independent existence. Only two thirds of all ulcers heal without amputation within 12 months and in these, the median time to healing is 78 days[2, 3]. Forty percent of patients whose ulcers heal will develop a recurrence within 12 months[4].

Ulcers of the heel present particular difficulties and it has often been said traditionally that 'Heel ulcers don’t heal'. Seven percent of heel ulcers result in amputation of the limb in diabetes and 20% persist until death[5]. Despite this, a single centre review of a consecutive series of 154 heel ulcers in 97 patients with diabetes managed in UK revealed that the eventual incidence of healing of heel ulcers without surgery was very similar to ulcers elsewhere on the foot. The median time to healing was, however, very much longer at 200 (24 to 1,225) days[5] - almost 3 times longer than ulcers elsewhere on the foot. A recent multicentre survey in 14 centres in Europe reported that the median time to healing of heel ulcers was very similar, at 237 days[6]. Heel ulcers in diabetes also differ from ulcers elsewhere on the foot in that they are frequently painful.

Many heel ulcers arise as a result of the pressure of immobilisation, and pressure ulcers are very common in acute hospitals. Repeated prevalence surveys in UK suggest that 8 to 10% of all patients in acute hospital beds develop a pressure ulcer, of which one third are on the heel; half of all pressure ulcers are in people with diabetes. The prevalence of pressure ulcers is higher in long-stay hospitals and care homes ([name], [name] unpublished data).

While the principles of care have been specified by the National Institute for Clinical Excellence (NICE) and the Royal College of Nursing (RCN)[7], and by the International Working Group on the Diabetic Foot (International Diabetes Federation)[8], there are no specific interventions which have been shown to improve the outcome. The use of a non-removable below-knee fibreglass (total contact or variant) cast is known to hasten healing in ulcers caused by abnormal pressure loading on other parts of the foot[9], but it has been reported to be ineffective when the ulceration is on the heel[10].

In the absence of specific treatment of proven effectiveness in heel ulcers, a small number of specialists in UK advocated the use of lightweight, removable fibreglass heel casts, and produced uncontrolled observational evidence that these devices result in both a reduced time to healing and a prompt improvement in pain and discomfort. Thus, healing was observed in 42 (84%) of a consecutive series of 50 heel ulcers (in patients both with and without diabetes, but all of whom had peripheral arterial disease), with a median (range) time to healing of 6 (3 to 13) weeks[11]. Although the apparent benefit seems greater than would be expected for such a simple device, the findings of this uncontrolled study are mirrored by the clinical impression of the applicants. The mechanism for any positive effect is not known but may relate to the reduction of shearing and stretching forces applied to the surface of the ulcer. Current strategies to reduce local forces in an area of ulceration (or ulceration risk) are largely concentrated an attempt to reduce vertical forces with minimal effect, if any, on shear and on stretching.

Lightweight fibreglass heel casts take approximately 15 minutes to mould to the heel and can be easily fashioned in a domiciliary setting. They are applied over the primary wound dressing and held in place with an outer dressing, being saved and re-used each time the dressing is changed. They are replaced when stained, damaged or lost, and can often be worn inside shoes. Health care professionals can be trained in their use in approximately 30 minutes, and the material cost of each cast is approximately £7. Casts need to be replaced on average every three weeks.

The purpose of the proposed study is to systematically evaluate the effectiveness and cost implications of this simple and apparently beneficial intervention. The study was funded by NHS National Institute for Health Research, Health Technology Assessment Programme Grant 09/01/53.

## Methods/Design

### Study configuration

This will be an observer-blind, randomised controlled trial. Randomisation will be stratified by ulcer grade (National Pressure Ulcer Advisory Panel-European Pressure Ulcer Advisory Panel (NPUAP-EPUAP) Grade 2, 3 or 4, see below) and by ulcer area (greater than or equal to 25 mm^2^ and less than or equal to 1 cm^2^ or greater than 1 cm^2^), using random permuted blocks of randomly varying size. Randomisation will be undertaken by Nottingham Clinical Trials Unit (CTU), using a web-based system.

#### NPUAP-EPUAP ulcer grading system

Non-blanchable erythemaPartial thicknessFull thickness skin lossFull thickness tissue lossUnstageable/Unclassified: full thickness skin or tissue loss - depthunknown

#### Primary endpoint

The primary endpoint will be percentage of all ulcers healed at or before 24 weeks (6 months). Healing will be defined as epithelialisation maintained for 4 weeks and will be confirmed by an observer blind to the randomisation group.

#### Secondary endpoints

(i)*Ulcer-related outcomes*

Time to healing, change in ulcer area (measured by both acetate tracings and digital images analysed by using appropriate software to define area), infection, major and minor amputation, ulcer recurrence, secondary ulceration on either limb and adverse device effects (ADEs).(ii)*Patient-related outcomes*

Local pain (visual analogue scale; VAS), Euroqol-5D (EQ-5D), Cardiff Wound Impact Schedule (CWIS), hospital admission (relating primarily either to the heel ulcer or not), hospital length of stay and death.(iii)*Cost-effectiveness*

Cost-effectiveness will be assessed by developing a decision-analytic model to estimate costs and health outcomes, including percentage of healed ulcers and Quality Adjusted Life Years (QALYs) gained. Costs will be compared between the two groups using a bottom-up approach from the perspective of UK NHS and personal social services. Data relating to the costs of training professionals and the costs of heel casts and their application will be collected by discussions with relevant clinical and finance staff. Incremental cost-effectiveness and cost-utility ratios will be generated for a series of time horizons (including a lifetime perspective) that reflect management of patients with diabetic ulcers of the heel. The findings will be subjected to a series of one-way sensitivity analyses to determine the degree to which variation in parameter estimates affect the relative cost-effectiveness ratios. The results will be used to model the likely effects over the particular time horizons and costs and effects will be discounted at 3.5%. A probabilistic sensitivity analysis will be conducted to investigate the joint uncertainty in parameter values and cost-effectiveness acceptability curves will be generated. A budget impact analysis will be undertaken for 1-year and 5-year periods and will compare the costs to the health service of the use of heel casts in the management of ulcers of the heel in diabetes.

#### Safety endpoints

The study population is one which comprises older aged people who will have a high prevalence of co-morbidities, including renal, cardiac and cerebrovascular diseases. Moreover, ulcers of the foot may themselves worsen and lead to hospital admission because of infection or increasing necrosis. Although no specific safety issues are foreseen with the use of the heel cast, significant events are listed among the secondary outcome measures. Other unexpected ADEs will be recorded and if considered serious (SADE) will be reported to the sponsor in accordance with the principles of Good Clinical Practice (GCP).

The trial will be stopped when the last recruited subject reaches the end of the trial. However, premature termination of the clinical trial may occur because of a regulatory authority decision, change in opinion of the Research Ethics Committee (REC), or safety problems at the discretion of the Data Monitoring Committee (DMC) or Sponsor. No formal interim analyses for efficacy are planned by the Trial Management group (TMG). However, the DMC may need to assess efficacy in relation to safety in order to advise the Trial Steering Committee (TSC) appropriately. Stopping for safety will be based on an informal assessment by the DMC of adverse events. To aid interpretation of efficacy, Haybittle-Peto type boundaries of ± 3 standard errors (*P* < 0.0027) will be adopted to permit the DMC to break the blind with negligible effect on the properties of the final analysis.

Recruitment at any centre may be stopped for reasons including low recruitment and inadequate data recording.

### Randomisation and blinding

Internet-based treatment assignment will be determined by a computer-generated pseudo-random code using random permuted blocks of randomly varying size, created by the Nottingham CTU. Trial participants will be allocated with equal probability to each treatment arm with stratification by ulcer grade and ulcer size.

Participants will be randomised to be managed either with usual care recommended by the RCN and NICE[7] (see below) or with usual care plus a fibreglass heel cup. For participants randomised to the intervention group, a fibreglass heel cast will be made according to agreed procedures by clinical research staff who have been trained to an agreed level of competence. Participants or carers will be provided with written and verbal instructions on its use. Dressings may be changed as often as patients/carers feel necessary but this will be at least twice weekly.

#### Components of usual care

Formal assessment of ulcer and surrounding skinProvision of any necessary off-loadingDebridement (i) sharp, (ii) other as appropriate (but excluding the use of larvae)Appropriate dressing productsAppropriate antibiotic therapyNutrition and self careOptimal glycaemic controlRevascularisation if deemed clinically necessaryContinued close observation

### Study management

This trial will be conducted in accordance with independent ethics committee (IEC), relevant informed consent regulations (Declaration of Helsinki), ISO-14155 Guidelines and the Data Protection Act 1998. In addition all local regulatory requirements will be adhered to, in particular those which afford greater protection to the safety of trial subjects. All investigators and research staff will be fully trained in GCP, and the study will be conducted in line with these principles. There will be an independent DMC and a TSC and both will be constituted according to Medical Research Council (MRC) guidelines. The study has been approved by the Yorkshire & The Humber - Leeds West National Research Ethics Committee (reference 10/H1307/124) under the UK National Integrated Research Application Scheme. All participants gave written informed consent.

### Duration of the study and participant involvement

The start date was 1February 2011. Recruitment was planned to continue until 31 August 2014 and the intervention phase planned to end 28 February 2015. Recruitment was terminated on 4 September 2014 by which time 509 participants had been recruited.

#### Duration of participant involvement

If the ulcer remains unhealed, participants will have fortnightly assessments by the researcher and will remain in the study for 24 weeks. If the ulcer heals, they will have two more fortnightly assessments. If the ulcer remains healed, they will then have only their 12-week and 24-week assessments, unless these have already been done. If the ulcer heals at 22 or 24 weeks, the participant will have two further fortnightly assessments to confirm healing.

#### End of the study

The study will end when the final patient has completed their final study visit.

### Selection and withdrawal of participants

#### Recruitment

Patients will have diabetes associated with an ulcer (NPUAP-EPUAP grades 2, 3 or 4 - see Table 1) on the heel (that is affecting the skin below the malleoli but overlying the calcaneum inferiorly, posteriorly, medially or laterally) and which has been present for at least 2 weeks. Those affected will be identified by the health care professionals usually caring for them in hospitals, care homes or the community. The presence of peripheral arterial disease, wound infection and other particular co-morbidities (such as end-stage renal failure of immobilisation) will not be regarded as specific contraindications.

**Table 1 Tab1:** **Fibreglass casts for heel ulcers in diabetes: trial profile**

	Screening visit	Visit 1 Randomisation	Visit 2	Visit 3	Visit 4	Visit 5	Visit 6	Visit 7	Visit 8	Visit 9	Visit 10	Visit 11	Visit 12	Visit 13
		Week 0	Week 2	Week 4	Week 6	Week 8	Week 10	Week 12	Week 14	Week 16	Week 18	Week 20	Week 22	Week 24
Check inclusion/exclusion criteria	**X**	**X**												
Information about study	**X**													
Informed consent	**X**													
Patient demographics		**X**												
ABPI		**X**												
Neuropathy		**X**												
Wound size by acetate tracing		**X**	**X**	**X**	**X**	**X**	**X**	**X**	**X**	**X**	**X**	**X**	**X**	**X**
Digital image after debridement		**X**	**X**	**X**	**X**	**X**	**X**	**X**	**X**	**X**	**X**	**X**	**X**	**X**
Cast applied if randomised to cast group		**X**	**X**	**X**	**X**	**X**	**X**	**X**	**X**	**X**	**X**	**X**	**X**	
Medication log		**X**	**X**	**X**	**X**	**X**	**X**	**X**	**X**	**X**	**X**	**X**	**X**	**X**
EQ-5D		**X**						**X**						**X**
CWIS		**X**						**X**						**X**
Pain VAS	**X**	**X**	**X**	**X**	**X**	**X**	**X**	**X**	**X**	**X**	**X**	**X**	**X**	**X**
Non-blinded Assessment			**X**	**X**	**X**	**X**		**X**	**X**	**X**	**X**	**X**	**X**	**X**
Collect health economic diary		**X**	**X**	**X**	**X**	**X**	**X**	**X**	**X**	**X**	**X**	**X**	**X**	**X**
Blinded assessment								**X**						**X**
							**Visit at which ulcer is judged healed**		**2 weeks after ulcer first judged healed**	**4 weeks after ulcer first judged healed**		**Visit 7 Week 12**		**Visit 13 Week 24**
Digital image after debridement							**X**		**X**	**X**		**X**		**X**
Cast applied if randomised to cast group							**X**		**X**	**X**		**X**		**X**
Medication log							**X**		**X**	**X**		**X**		**X**
EQ-5D												**X**		**X**
CWIS												**X**		**X**
Pain VAS							**X**		**X**	**X**		**X**		**X**
Non-blinded assessment							**X**		**X**	**X**		**X**		**X**
Collect health economic diary							**X**		**X**	**X**		**X**		**X**
Blinded assessment							**X**			**X**		**X**		**X**

If an ulcer is judged healed on or before Week 24, then healing should be confirmed by a blinded assessor as soon as possible, and within 4 days. If the ulcer breaks down within 4 weeks of first being judged healed, the participant should continue in the study. If the ulcer remains healed, the participant needs to have 12 Week and 24 Week visits – unless these have already been done. ABPI, ankle brachial pressure index; CWIS, Cardiff Wound Impact Schedule; EQ-5D, Euroqol-5D; VAS, visual analogue scale.

#### Screening log

A log will be kept at each centre which will list patients screened but not included in the study. The data kept in the log will include only the date of screening, patient initials, age and reason for screen failure. The log will not leave the clinical centre and the only data collected from the centre will be the absolute numbers of patients screened patients and the reasons for screen failure.

#### Inclusion criteria

Type 1 or type 2 diabetes mellitusAge 18 years or overAn ulcer of the heel (below the malleoli and affecting the skin overlying the calcaneum) of NPUAP-EPUAP Grade 2 to 4, which has been present for 2 or more weeks and which has a cross-sectional area ≥ 25 mm^2^. If there is more than one heel ulcer, one - which will be the largest or that judged most clinically significant - will be selected as the index ulcerSubjects who are both able and willing to give written informed consent

#### Exclusion criteria

Frailty or disability which would mean that participation in the study might have an adverse effect on patient well-being and moodThe need for any off-loading device to be non-removableThe likelihood of protocol violation because of planned travelThose who withhold consentActive participation in another study of a wound care productThe use of topical negative pressure or application of larvae to the index heel ulcer

### Study procedure

#### Study device

The study device is a fibreglass heel cast, moulded to the shape of the heel and split for easy removal and replacement. The heel cast will be made according to a study specific procedure and applied over the primary dressing (and secondary dressing if appropriate) which will be selected at the discretion of the patient’s usual carer. The cast will be covered by a single layer of Softbanor equivalent bandage and held in place by a retention layer. Written instructions on device usage will be given to patients and care givers. Heel casts will be replaced when worn or stained.

#### Study plan

Participants who give written informed consent will be asked either to attend a research clinic, or will have the necessary information and examination at another venue which is convenient for them and their carer.

The following procedures will be performed at the appropriate visit(s)*Prior to randomisation visit*

The nature of the study will have been explained to the patient/carer by their usual doctor/nurse/podiatrist2.*Randomisation visit 1* (*week 0*)

Check inclusion and exclusion criteria

Explain study to patient

Written informed consent/agreement

Documentation of demographics and baseline clinical details, including:

Assessment of neuropathy (loss of protective sensation) using a 10 g monofilament applied to three sites (hallux, first and fifth metatarsal heads) on the sole of the index footAssessment of peripheral arterial disease by palpation of pedal pulses and ankle brachial pressure index (ABPI)Ulcer grade by NPUAP/EPUAPDigital image of ulcer following any necessary debridementLocal pain assessment by VASPatient well-being and function documented using EQ-5D and Cardiff Wound Impact Schedule (CWIS)Documentation of medicationTracing of ulcer area with acetate sheet for the purposes of randomisation and stratification

#### Randomisation

3.*Visits 2to 13 will be every 2 weeks* (*±4 days*) *to 24 weeks* (*visit 13*)

During each visit a check will be made for healing. If the ulcer is judged healed, it will be confirmed by blinded a clinician within 4 days. It will then be reviewed after two weeks (±4 days) weeks and 4 weeks (±4 days). If the ulcer is thought to remain healed at 4 weeks, healing will be confirmed once more by a blinded clinician. If the ulcer recurs during this period, the participant should return to the intervention phase of the study. If the ulcer does not recur, the participant should continue to collect data for health economic analysis and should be reviewed by the research staff at 12 and 24 weeks, assuming these dates have not already passed.

Other measures to be taken at different visits are charted in Table 1. The wound will be cleaned, debrided (when appropriate), traced and imaged at each visit before being redressed. Patient well-being and function will be documented by completion of EQ-5D and CWIS (weeks 12 (±1) and 24 (±2) only.

For participants randomised to the intervention group, a fibreglass heel cast will be replaced as necessary by trained personnel and the patient/carer will be given written and verbal instructions on its use.

### Protocol violations

The following will be regarded as a protocol violation:

Failure to use the study intervention (fibreglass heel cast) as recommended for more than 7 consecutive days, or for more than a cumulative total of 14 days during the course of the 24 week study. Those who violate the protocol in this way alone will not be withdrawn but will continue with fortnightly visits

The following will be regarded as a protocol violation necessitating withdrawal from the study:

Omission of more than one consecutive scheduled fortnightly assessment by the researcher, or omission of a total of 3 or more of these visits during the 24 week study, or until healing is confirmed

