### Withdrawals

A patient can be withdrawn from the study if:

Consent/agreement is withdrawnThe participant loses capacityIt is found that they were recruited in errorThey have omitted more than one consecutive scheduled fortnightly assessment by the researcher, or omitted a total of three or more of these visits during the 24 week study, or before healing is confirmedThe participant is lost to follow-up

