### Statistical analysis

Appropriate descriptive statistics will be presented for each variable. Two-sided statistical test will be performed and presented with exact *P*-values, with interval estimates constructed using 95% as the level of confidence.

Descriptive statistics, analytical methods and sample size considerations will be included. The study team together with the investigators will make the decisions regarding individual values belonging to a patient to be excluded from the analysis; for example, out of range values/values that cannot be objectively verified. The investigators will make the final decision regarding coding on the reason(s) for withdrawal. The safety population (SP) will comprise all randomised patients for the study

The intention-to-treat (ITT) population is defined as all subjects who were randomised. Given the study is based on a population with an expected high morbidity, the attrition rate will be monitored closely. If the missing primary outcome data fall within the 20 to 25% level, then ITT will be completed without imputation in the first instance and repeated with multiple imputation as a sensitivity analysis. ITT is equal to SP in this study. Once a participant has a healed wound, which is confirmed as ‘healed’, they will no longer participate in the intervention phase of the study, as they will have achieved the primary outcome. Such participants will be deemed to have completed their participation in the efficacy part of the study and their data will be included in the numbers ‘healed’ by 24 weeks.

Per protocol (PP) population is defined as a subset of ITT population that has completed the treatment period of maximum 24 weeks according to the protocol. The following will be regarded as a protocol violation necessitating exclusion from the PP analysis:

Failure to use the study intervention (fibreglass heel cast) as recommended for more than 7 consecutive days, or for more than a cumulative total of 14 days during the course of the 24-week studyOmission of more than one consecutive scheduled fortnightly assessment by the researcher, or omission of a total of 3 or more of these visits during the 24-week study

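### The missed-visit withdrawal rule can remove only participants not yet confirmed healed, so it tends to overstate the percentage healed; two sections also disagree on whether it is mandatory

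*Protocol article*

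**What the plan says.** Protocol violations, in the protocol article, introduces the rule with "The following will be regarded as a protocol violation necessitating withdrawal from the study". The trigger is "Omission of more than one consecutive scheduled fortnightly assessment by the researcher, or omission of a total of 3 or more of these visits", and the count of three or more is taken over omissions "of these visits during the 24 week study, or until healing is confirmed".

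Withdrawals repeats the trigger for those who "have omitted more than one consecutive scheduled fortnightly assessment by the researcher", but under the permissive opening "A patient can be withdrawn from the study if".

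Protocol violations treats non-use of the cast differently: "Those who violate the protocol in this way alone will not be withdrawn but will continue with fortnightly visits".

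Statistical analysis states: "The intention-to-treat (ITT) population is defined as all subjects who were randomised". It lists the same missed-visit trigger as a reason for exclusion from the per-protocol analysis. If 20 to 25% of primary outcomes are missing, "then ITT will be completed without imputation in the first instance and repeated with multiple imputation as a sensitivity analysis".

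The rule set under Primary outcome counts a confirmed healer as healed whether or not that person attends at week 24, and names amputation of the target limb as a failure. It does not classify a participant withdrawn for missed visits. Table 1 schedules a blinded assessment at week 24.

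**The concern.** Two things are wrong with the rule as written. First, one section requires withdrawal and the next merely allows it, so sites could apply it differently.

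Second, exposure to the rule depends on the outcome. A participant whose ulcer never heals is exposed at all 12 post-baseline visits. One who heals early is exposed at fewer, and after confirmation cannot become missing for the primary endpoint at all. Even if everyone misses visits at the same rate, more non-healers than healers are removed. The Discussion expects frequent intercurrent illness and hospital admission in this population, which could strengthen the link between missed visits and poor outcome.

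If outcomes are not sought after withdrawal, the analysis without imputation uses a set enriched for healers. The percentage healed is the stated primary endpoint and also feeds the cost-effectiveness model. Inflating the sample size for attrition protects power but does not remove this bias.

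**Working it through.** **The plan's own figures.** Inputs from Determination of sample size: 40% v 55%, α 0.05, power 80%; two-sided testing is from Statistical analysis. The pooled-variance formula gives (1.960·√(2·0.475·0.525) + 0.842·√(0.40·0.60 + 0.55·0.45))² / 0.15² ≈ 172.8, or 173 per arm. With continuity correction, (172.8/4)·(1 + √(1 + 4/(172.8·0.15)))² ≈ 185.9, or 186, as stated. Then 372/0.70 = 531.4 and 372/0.75 = 496. The sample size reproduces and is not at fault.

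**Chance of meeting the trigger.** Let V be the number of visits at risk and m the chance of missing each, independently. The documents give no miss rate, so m is an assumption. The trigger is avoided with no miss, one miss, or two non-adjacent misses:

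P(trigger) = 1 − [(1−m)^V + V·m·(1−m)^(V−1) + C(V−1, 2)·m²·(1−m)^(V−2)]

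Example, V = 12, m = 0.10: 1 − (0.2824 + 0.3766 + 0.1918) = 0.149.

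| m | V = 6 | V = 8 | V = 10 | V = 12 |
|---|---|---|---|---|
| 5% | 1.2% | 1.9% | 2.6% | 3.6% |
| 10% | 4.9% | 7.5% | 10.9% | 14.9% |
| 15% | 10.6% | 16.5% | 23.5% | 31.3% |

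Non-healers have V = 12 (visits 2 to 13). For healers, V runs to confirmation, four weeks after the ulcer is first judged healed. So V = 6, 8 and 10 mean first judged healed at week 8, 12 and 16. These values are also assumptions.

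**Effect on the percentage healed.** Suppose withdrawn participants have no outcome and are left out. With true healing h, and w_h and w_u the trigger probabilities for healers and non-healers:

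observed = h(1−w_h) / [h(1−w_h) + (1−h)(1−w_u)]

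observed OR = true OR × R(cast)/R(control), where R = (1−w_h)/(1−w_u)

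The true OR is (0.55/0.45)/(0.40/0.60) = 1.83. If R is the same in both arms, it cancels.

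Example, healer V = 6, misses 15% control and 10% cast:
- Control: 0.40·0.8939 = 0.3576; 0.60·0.6871 = 0.4123; observed 46%.
- Cast: 0.55·0.9513 = 0.5232; 0.45·0.8508 = 0.3828; observed 58%.
- OR = (0.5232/0.3828)/(0.3576/0.4123) = 1.58.

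| Misses, control/cast | Healer V | Observed healed (true 40% v 55%) | OR (true 1.83) | OR under no effect (40% in both arms) |
|---|---|---|---|---|
| 10%/10% | 6 | 43% v 58% | 1.83 | 1.00 |
| 10%/10% | 8 | 42% v 57% | 1.83 | 1.00 |
| 10%/10% | 10 | 41% v 56% | 1.83 | 1.00 |
| 15%/15% | 8 | 45% v 60% | 1.83 | 1.00 |
| 15%/10% | 6 | 46% v 58% | 1.58 | 0.86 |
| 15%/10% | 8 | 45% v 57% | 1.64 | 0.89 |
| 15%/10% | 10 | 43% v 56% | 1.73 | 0.94 |
| 10%/15% | 6 | 43% v 61% | 2.13 | 1.16 |
| 10%/15% | 8 | 42% v 60% | 2.05 | 1.12 |
| 10%/15% | 10 | 41% v 58% | 1.95 | 1.06 |

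**Reach of the planned imputation.** With healer V = 8 and 10% misses in both arms, the rule alone withdraws 12.0% of controls (0.40·7.5% + 0.60·14.9%) and 10.9% of the cast arm. That is below the 20 to 25% band to which multiple imputation is tied. At 15% misses the shares are 25.4% and 23.1%. Losses from other causes would add to these.

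**The case against.** Several stronger readings are tempting, and the article does not support them.

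- **That withdrawal is simply compulsory.** Withdrawals says such participants may be withdrawn. What is established is a contradiction between two sections.
- **That the intention-to-treat analysis is declared to be a complete-case analysis with non-healers deleted.** It is defined on everyone randomised. Using missed visits as a per-protocol exclusion presupposes that these people still count in it, and the time-to-healing analysis censors unhealed participants at trial exit or last assessment. Nothing says outcome collection stops at withdrawal. The loss of outcome is inferred from withdrawal from the study, no imputation first, and no stated rule for these cases. The full protocol or analysis plan may deal with it.
- **That the odds ratio is biased in a known direction.** With equal miss rates it is not biased in this model. With unequal rates it can move either way.
- **That cast replacement makes the cast arm attend better.** Both arms share the same fortnightly schedule, and casts are dealt with at those visits. The only support for differential attendance is that participants and carers are unblinded, which makes it possible in either direction.
- **That using the attrition allowance is itself a defect.** Attrition is what the allowance is for.

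Healer exposure also matters. Background reports median healing times of 200 and 237 days for heel ulcers, so healing within 24 weeks may come late. At 10 healer visits and 10% misses, the overstatement is only about one percentage point.

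These points limit the size and certainty of the concern. They do not remove the asymmetry, which follows from the rule's end point and from how confirmed healers are counted.

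**Conclusion.** The concern holds in a limited form. The two sections conflict on must versus may. The rule also ties removal to not yet being confirmed healed, which tends to raise the observed percentage healed in both arms. The rise is about 1 to 3 percentage points at 10% missed visits, and about 5 points at 15% with 8 healer visits.

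The odds ratio of 1.83 is unaffected when miss rates are equal between arms. With 15% in control and 10% in the cast arm it falls to 1.58–1.73 across 6 to 10 healer visits. With the reverse it rises to 2.05–2.13 at 8 to 6 healer visits (1.95 at 10).

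All of this assumes independent misses, the stated miss rates and exposures, and no outcome obtained after withdrawal. None of these is given in the article. The direction of the effect on the percentages is well founded; the sizes are illustrations.

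**What to change.** Remove missed visits as a reason for study withdrawal from both Protocol violations and Withdrawals. Keep them only as the per-protocol exclusion already listed in Statistical analysis. This mirrors how non-use of the cast is handled, and concerns follow-up and data only.

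For these participants, obtain the week-24 blinded assessment that Table 1 already schedules, with the four-week confirmation where needed, and include them in the intention-to-treat analysis. State there how healing is classified when it cannot be observed.

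Recruitment closed on 4 September 2014 with 509 randomised, so the change applies to participants still within follow-up. For anyone already withdrawn for missed visits alone who has not withdrawn consent, seek week-24 healing status where it can still be established.

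The cost is some extra contact effort with poor attenders. Recovery will be limited for those past week 24, because late contact may not establish blinded confirmation of healing held for four weeks. Report the number withdrawn under this rule by arm, so that readers can judge what remains.
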